## 3. Rehabilitation

### 3.1. Cognitive RehabilitationRehaCom Modules

#### RehaCom Modules

CR training will be performed by the computerized program RehaCom [15,16,17,18,19,20,21,22,23]. This program will be installed on a laptop with an external mouse attached. The sections of the program used to rehabilitate memory deficits will be:*Strategic memory training (LEST)*: The patient will be presented with a pair of words on the PC screen to memorize (the number of words could increase or decrease according to the performance of the subject). The task will be to find the objects that correspond to the memorized words. When the patient recognizes an object, he will have to click on it and repeat the operation until he/she has clicked on all recognized objects. The task will end when all the objects are identified. The correct choice will be marked in green, the wrong one in red. For each group of images presented, the subject will have three possibilities of error, after which the exercise will return to the opening words and the patient is asked to memorize them again. The words to be memorized will change only when all the images are recognized without making mistakes. Patients can use any personal memorization strategies: some will memorize the words according to the presentation order, others by dividing them into semantic categories and others by building stories. Between memorizing words and recognition, participants will be asked to perform a distracting task: move a basket from one side of the screen to the other to collect all the fruits that fall from a tree.*Working memory (WOME)*: The patient will be presented with three decks of cards (a deck of poker cards, a deck of colored cards and one characterized by unusual symbols) from which he/she can choose his/her favorite. Then, the program asks the patient to follow some specific indications (e.g., to memorize all the cards presented, to memorize the cards in the presentation order, and to memorize only cards with certain characteristics). In the event that the patient does not perform the exercise correctly, this will be repeated a second time with the same cards. To increase the difficulty of the exercise, a distractor (e.g., a question of general knowledge) may be introduced between the memorization of the cards and their recognition.*Figurative memory (BILD)*: Words to be memorized without time limits will appear on the PC screen. Once all the words are memorized, the patient will see a series of figures moving across the screen from right to left. When the patient sees one of the figures, corresponding to the objects memorized before, passing through a red highlighted area, he must press the “ok” button. The number of figures will progressively increase with the improvement of the patient’s performance.*Verbal memory (VERB)*: The patient will see a short text in which he/she has to memorize names, numbers, objects and events. Subsequently, the subject is asked to answer some questions about what has been read, choosing from four answer options. The difficulty of the task may decrease or increase by varying the length of the passage and the amount of information depending on the patient’s performance. Furthermore, the settings of the task can be changed: for example, the exercise can be set in such a way as to have the patient read two passages, one after the other, and then answer questions asked about the first one, or the patient can be asked to answer with open answers.

### 3.2. Motor Rehabilitation

Diversified and specific rehabilitation sessions will be planned for each patient, paying particular attention to motor disabilities of the lower limbs, most commonly observed and complained of by almost all patients with MS. In this regard, exercises will mainly be applied to improve: decreased range of motion, spasticity, balance disorders, coordination problems, reduced postural control, strength deficit, impaired sensitivity, motor difficulties in walking and in the transition from sitting to standing and vice versa.

The proposed exercises are presented in the Supplementary Materials section.

## 4. Statistics and Outcome

### 4.1. Data Analysis

The sample size has been determined based on an a priori power analysis, using the software G*Power 3.1 [56], with a 0.30 effect size, power of over 0.95, and an alpha level of 0.05, as being sufficient for both repeated measures, within–between interaction Analysis of Variance (ANOVA). The minimum number of participants required is 48 (16 participants for each group), but we have decided to reach a total number of 60 participants (20 participants for each group) in order to avoid possible drop-out effects.

For the purposes of this study, different types of statistical analysis will be carried out using SPSS 18 (SPSS Inc., Chicago, IL, USA) and a significant threshold throughout this study will be set at *p* < 0.05.

Statistical analysis will be of two types:“Within-group” analyses. These statistical analyses will be aimed at evaluating any improvement in patients’ cognitive performance. Within each group of patients, the assessments at T0 will be compared with that at T1 and T2 through a repeated measures ANOVA between the scores of the cognitive assessments. In case of significance, post hoc tests will be carried out to which a Bonferroni correction will be applied with significance set at *p* < 0.016. Similarly, the same analysis will be conducted to compare the levels of anxiety and depression, the self-perception of cognitive deficit and the level of perceived disability.“Between-group” analyses. These statistical analyses will be aimed at comparing the results obtained by the groups at T0, T1, and T2 by performing an ANOVA between the scores of the cognitive assessments. In case of significance, post hoc tests will be performed to which a Bonferroni correction will be applied with significance set at *p* < 0.016. Additionally, in this case, the same comparative analysis will be carried out on the following variables: levels of anxiety and depression, self-perception of one’s cognitive difficulties and level of perceived disability.

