## 2. Materials and Methods

### 2.1. Aim, Design and Setting of This Study

This study has the following primary objectives:Compare three forms of rehabilitation—cognitive, motor and combined (cognitive–motor)—in three groups of MS patients.Check whether a combined rehabilitation approach can induce a significantly greater improvement on memory efficiency of MS patients, than cognitive rehabilitation performed alone.

Secondary objectives:Evaluate whether self-perception and objective improvement correspond.Evaluate the impact of each rehabilitation program on patients’ overall disability.Monitor the effects of the three rehabilitation conditions after 6 months.

This study will be a single-blind parallel controlled clinical trial, in which each subject will be randomly assigned to a single treatment. The study protocol will be divided into an initial evaluation by standardized tools of clinical, cognitive, emotional, quality of life and functional self-perception state, at time 0 (T0). Subsequently, patients will be assigned to one of the three conditions and will undergo rehabilitation treatment for a total of 12 weeks (two sessions each week). At the end of the treatment, each patient will undergo an overall re-evaluation (T1) with parallel forms of the tools used at T0. After 6 months, all patients will be submitted to a further overall re-evaluation as a follow-up measurement of each treatment (T2). The examiner carrying out pre- and post-treatment evaluations will be different from the one carrying out the rehabilitation process in order to avoid any individual bias. Figure 1 shows the study flowchart.

Patients in charge of both the “Santa Lucia” Neuroscience and Rehabilitation Foundation (Rome) and the “Filippo Turati” Foundation (Rome) will be recruited. All evaluations and rehabilitation training will be conducted at the laboratory and in the rehabilitation sites of the two centers by adequately trained neurologists/physiatrists, psychologists and physiotherapists.

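### The interaction test used to size the trial is not among the analyses listed in section 4.1, so the stated power of over 0.95 cannot be read as the power of the between-arm comparison or of primary objective 2

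*Protocol article*

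**What the plan says.** Section 4.1 (Data Analysis) gives the sample-size inputs as "with a 0.30 effect size, power of over 0.95, and an alpha level of 0.05", described "as being sufficient for both repeated measures, within–between interaction Analysis of Variance (ANOVA"). The result is stated as "The minimum number of participants required is 48 (16 participants for each group"), and then "we have decided to reach a total number of 60 participants (20 participants for each group") to allow for drop-out.

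The same section then divides the analysis into two types. The first is a repeated-measures ANOVA over T0, T1 and T2, carried out within each group. The second is between groups: "These statistical analyses will be aimed at comparing the results obtained by the groups at T0, T1, and T2 by performing an ANOVA" on the cognitive scores. Both are followed by Bonferroni post hoc tests at p < 0.016. Neither description mentions a group-by-time interaction, a change score or an adjustment for T0.

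Section 2.1 gives two primary objectives: to compare the three forms of rehabilitation, and to "Check whether a combined rehabilitation approach can induce a significantly greater improvement on memory efficiency of MS patients, than cognitive rehabilitation performed alone".

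**The concern.** The article states both the test that was powered and the tests that will be run, and they differ. Objective 2 concerns a difference in change between two arms. A significant T0-to-T1 gain in one arm and a non-significant gain in another does not test that difference. A comparison of raw scores between arms at a visit uses neither change nor baseline.

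The "power of over 0.95" is therefore attached to no listed analysis. A reader who takes it as the power for combined versus cognitive training on memory could read a null result as evidence that the two are equally good. The article gives no basis for that.

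**Working it through.** **Inputs.** From section 4.1: effect size 0.30, alpha 0.05, three groups, N = 48 or 60 (16 or 20 per arm), post hoc threshold 0.016. Not stated, so assumed: 0.30 is Cohen's f in G*Power's default convention; number of measurements m; correlation between visits ρ; sphericity.

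**1. The stated 48.** For the within-between interaction with k = 3 groups, λ = f²·N·m/(1−ρ), df1 = (k−1)(m−1), df2 = (N−k)(m−1).

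| m | ρ | N | Power |
|---|---|---|---|
| 2 | 0.5 | 45 | 0.945 |
| 2 | 0.5 | 48 | 0.958 |
| 2 | 0.5 | 60 | 0.987 |
| 3 | 0.5 | 36 | 0.944 |
| 3 | 0.5 | 39 | 0.962 |
| 3 | 0.35 | 45 | 0.939 |
| 3 | 0.35 | 48 | 0.954 |

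So 48 is the smallest multiple of 3 with power above 0.95 for m = 2, ρ = 0.5, where λ = 0.09 × 48 × 2/0.5 = 17.28. It is equally so for m = 3, ρ of about 0.35. The figure reproduces, but the setting used cannot be identified.

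**2. What interaction f = 0.30 means between arms.** Take two visits and equal T0 means. If the arm deviations at T1 are a, the interaction effects are ±a/2, so the interaction f is half the between-arm f at T1. Interaction f = 0.30 is thus f = 0.60 at T1. In SD units:
- evenly spaced arms, f = d/√6: extremes differ by 0.60 × √6 = 1.47 SD, adjacent arms by 0.73 SD;
- one arm apart from two equal arms, f = d√2/3: d = 0.60 × 3/√2 = 1.27 SD.

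**3. The between-arm ANOVA at one visit.** λ = f²·N, df = 2 and N−3, alpha 0.05.

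| Meaning of 0.30 | f at T1 | N = 48 | N = 60 |
|---|---|---|---|
| Interaction f (m = 2, ρ = 0.5, equal baselines) | 0.60 | 0.958 | 0.987 |
| Between-arm f at one visit | 0.30 | 0.419 | 0.514 |

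In the first row λ at N = 48 is 0.36 × 48 = 17.28, the same as for the interaction test, so the two tests have equal power. In the second row the interaction f is 0.15, λ = 0.0225 × 48 × 2/0.5 = 4.32 = 0.09 × 48, and the interaction test also has 0.419 (48) and 0.514 (60). At ρ = 0.7 it would have 0.637 and 0.747.

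**4. Reha 2 versus Reha 1 at two-sided 0.016.** Noncentral t with noncentrality d·√(n/2) and 3n−3 df.

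| True difference of this pair | 16 per arm | 20 per arm |
|---|---|---|
| 1.47 SD (the pair are the extremes, T1 f = 0.60) | 0.95 | 0.98 |
| 1.27 SD (one of the pair stands apart, T1 f = 0.60) | 0.86 | 0.93 |
| 0.73 SD (evenly spaced, pair adjacent, T1 f = 0.60) | 0.35 | 0.44 |

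80% power needs about 1.19 SD (16 per arm) or 1.06 SD (20 per arm). The adjacent case would arise if motor training alone came lowest on memory, cognitive training in the middle and combined training highest. That ordering is an assumption. It is compatible with the Discussion, which hopes that combined training exceeds cognitive training alone on memory.

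**The case against.** A reader might infer that moving from the interaction test to the between-arm ANOVA cuts the power from over 0.95 to 42–51%. The documents do not support that. The 42–51% appears only when 0.30 is re-read as a between-arm f at one visit. Kept on the interaction scale for which it was entered, with two measurements, correlation 0.5 and equal baselines, the T1 ANOVA has the same 0.96 to 0.99. The gap comes from the effect-size scale and not from the change of test. This stands in full, and it rules out calling the stated sample size an arithmetic error.

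Two other points stand in part. First, the between-group sentence is loose, and a mixed ANOVA is not strictly excluded; a condensed article may also leave model terms to a fuller document. However, the division into two types of analysis, one of them within each group, favours separate analyses, and the article does commit itself to what it lists. If a mixed model is intended, saying so is the same edit. Second, replacing the three-arm comparison by one pairwise contrast would narrow primary objective 1, so the three-arm test has to stay.

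A reader might also count it as an error that three visits at correlation 0.5 need only 39 patients. Under that setting 48 is conservative, so it is no defect.

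**Conclusion.** The point holds as a mismatch between the powered test and the listed tests, and as a power statement that cannot be interpreted. No listed analysis directly tests a difference in improvement between Reha 2 and Reha 1.

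The power of the between-arm comparison at T1 is 0.96–0.99 or 0.42–0.51 (48–60 patients), depending on a scale the article does not give. On the favourable reading, the figure presupposes a largest difference of about 1.27–1.47 SD between active treatments, which the article neither states nor justifies. Even then, omnibus power does not carry over to objective 2: for that pair at 0.016 it runs from 0.35–0.44 to 0.86–0.98, according to how the three means are arranged.

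These values rest on G*Power's default convention and, for the conversion to T1, on two measurements, correlation 0.5 and equal baselines. The mismatch itself rests on none of them.

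**What to change.** In section 4.1, name one analysis for each primary outcome: a mixed model with group, visit and group-by-visit in which the interaction is tested, or a comparison of arms at T1 and T2 adjusted for T0. Keep the three-arm comparison for objective 1. For objective 2, specify the Reha 2 minus Reha 1 contrast in change on memory. The within-arm ANOVAs can stay as description.

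Replace "power of over 0.95" with the power of the named tests, including that contrast. State the difference in SD units, the number of measurements and the correlation assumed, and say on which scale 0.30 is expressed.

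No extra patients are proposed. The cost is rewording, and a stated power for objective 2 that is likely to look less favourable.

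### The two listed analyses do not carry forward the group-by-time test used for sizing, and the between-arm ANOVA makes no stated use of T0 scores

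*Protocol article*

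**What the plan says.** Section 2.1 of the protocol article gives as its second primary objective: "Check whether a combined rehabilitation approach can induce a significantly greater improvement on memory efficiency of MS patients, than cognitive rehabilitation performed alone". This is a comparison of change between two named arms.

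Section 4.1 sizes the trial "with a 0.30 effect size, power of over 0.95, and an alpha level of 0.05", for a repeated-measures "within–between interaction Analysis of Variance (ANOVA"). The stated minimum is 48, raised to 60 (20 per arm) to allow for drop-out.

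Section 4.1 then sets out two types of analysis:

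- **Within-group**, the only type described as assessing improvement: "Within each group of patients, the assessments at T0 will be compared with that at T1 and T2 through a repeated measures ANOVA".
- **Between-group**: "These statistical analyses will be aimed at comparing the results obtained by the groups at T0, T1, and T2 by performing an ANOVA" of the assessment scores.

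Both are followed by Bonferroni post hoc tests at p<0.016. Neither description mentions a group-by-time term, a between-arm comparison of change or a T0 covariate. Section 2.4 places randomisation after the baseline assessment.

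**The concern.** The objective and the sample size both concern a difference in change between arms. Of the listed analyses, one examines change without a comparator and the other compares arms without a stated use of where each patient started.

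Two things are at stake. The main comparison may be less precise than the data allow, and a chance difference at T0 stays in the estimate although T0 is measured before randomisation. Also, the only analysis labelled as measuring improvement cannot rank the arms, so a reader who relies on it for the comparative objective could be misled. A significance test between arms at T0 adds nothing, because randomisation makes its null hypothesis true.

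**Working it through.** **Inputs from section 4.1:** three arms, f=0.30, alpha 0.05, power above 0.95, N=48 minimum and 60 planned (20 per arm), post hoc threshold 0.016. **Not in the document:** the correlation r between a patient's scores at two visits, and the number of measurements m used for sizing. Both are assumptions here and are varied.

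**1. Reproducing N=48.** For the within–between interaction with k arms, the noncentrality is λ = f²·N·m/(1−r), with df (k−1)(m−1) and (N−k)(m−1). With k=3, m=2, r=0.5 and N=48: λ = 0.09×48×2/0.5 = 17.28, df 2 and 45, power 0.958. At N=45 power is 0.945, so 48 is the smallest balanced number above 0.95. With m=3, the number of visits planned, r=0.5 gives 39, r=0.4 gives 45 and r=0.3 gives 51. The stated figure therefore matches the interaction test at m=2 and r=0.5, or at m=3 with some r between 0.3 and 0.4.

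**2. Chance imbalance at T0.** With 20 per arm the SD of a difference between two arm means is √(2/20) = 0.32 SD. A gap above 0.3 SD arises in 34% of trials and above 0.5 SD in 11%.

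**3. Power of the three-arm test at T1.** Score-only ANOVA: λ = f²·N, df 2 and N−3. ANCOVA with T0: λ = f²·N/(1−r²), df 2 and N−4.

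*Reading A: 0.30 is the between-arm effect on T1 scores, N=60.*

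| Analysis | λ | Power |
|---|---|---|
| Score only | 0.09×60 = 5.40 | 0.51 |
| ANCOVA, r=0.3 | 5.40/0.91 = 5.93 | 0.55 |
| ANCOVA, r=0.5 | 5.40/0.75 = 7.20 | 0.64 |
| ANCOVA, r=0.7 | 5.40/0.51 = 10.59 | 0.82 |

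A plain change-score test has error variance 2(1−r) times that of the score. Its power is 0.38, 0.51 and 0.75 for the same three values of r, so it is not a dependable repair.

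*Reading B: 0.30 is the two-time interaction effect.* With equal T0 means, the arm effects at T1 split into minus half at T0 and plus half at T1. The T1 between-arm f is then 2×0.30 = 0.60. Score-only λ at N=48 is 0.36×48 = 17.28, power 0.958. At N=60 it is 21.6, power 0.987. ANCOVA at r=0.5 gives 0.990 and 0.998.

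**4. What within-arm tests can show.** Suppose every arm truly changes by 0.5 SD from T0 to T1, with r=0.5. The SD of change is √(2(1−0.5)) = 1 SD. A paired t test with n=20 at p<0.016 has noncentrality 0.5×√20 = 2.24 and power p = 0.366. Two identical arms then differ in significance with probability 2p(1−p) = 2×0.366×0.634 = 0.46. Three arms fail to agree with probability 1−p³−(1−p)³ = 0.70.

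**The case against.** A reader might infer that neither analysis tests the objective at all, or that the plan is invalid. The documents do not support that. Randomisation follows T0, so expected T0 means are equal and the expected T1 difference between Reha 2 and Reha 1 equals the expected difference in change. The post hoc contrast after the between-group ANOVA is therefore an unbiased test of the objective. Chance T0 imbalance is sampling error that its standard error already covers, and for one outcome at one visit it falsely separates two identical arms in only about 1.6% of trials. This stands in full.

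A reader might also take 46% and 70% as error rates of the plan. They are not. They describe inferring superiority from significance in one arm and not in another. The plan never states that inference and assigns comparison of arms to the between-group analysis.

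Three further points:

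- The sample-size sentence names the interaction, and the between-group sentence could be read as one mixed ANOVA over all visits. That reading is possible, but the wording does not settle it, and the interaction appears in neither listed analysis.
- Section 2.1 specifies parallel forms at T1, which reduces item-specific practice, and Table 1 sets no cognitive threshold that would select low scorers. Practice and regression to the mean should therefore not be pressed hard.
- Covariates are often left to an analysis plan. Here, however, the protocol does describe its analyses, and they do not match the test it was sized on.

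**Conclusion.** The point holds as a mismatch to correct and an improvement that costs almost nothing. It does not show an invalid analysis. The interaction that reproduces N=48 is not carried into the listed analyses, and the between-arm comparison makes no stated use of T0.

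The gain in power is uncertain. At N=60 it runs from 0.51 to between 0.55 and 0.82 under Reading A (r from 0.3 to 0.7). Under Reading B at r=0.5 it is about one percentage point, from 0.987 to 0.998. The document attaches 0.30 to the interaction, which favours Reading B, but it gives no r. Under both readings, adjustment corrects chance T0 imbalance, and within-arm tests remain unable to support a claim that one arm is better than another.

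**What to change.** In section 4.1:

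- Make the main between-arm analysis an ANCOVA of the T1 score, and separately of the T2 score, on arm, T0 score and the randomisation factors, or an equivalent baseline-adjusted mixed model.
- Report the adjusted Reha 2 minus Reha 1 difference in memory with its 95% CI as the answer to the second primary objective.
- Present within-arm changes as descriptive.
- Drop the between-arm significance test at T0.
- Align the sample-size paragraph with the analysis named, stating the assumed correlation and the number of measurements.

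The data and the planned N=60 stay as they are. The cost is one degree of freedom for T0 plus a few for the randomisation factors. Taking the four age bands that the 18–65 limit leaves usable, disease course, and sex if it is used, that is 3+1+1 = 5. With 60 patients, 60−3−1−5 = 51 residual degrees of freedom remain.

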
### 2.4. Randomization

After having completed the assessment procedures, the participants will be randomized to the three rehabilitation arms. The randomization assignment will foresee a stratification by age groups (<30; 30–40; 41–50; 51–65; >65) and will be weighted with respect to the variable phenotype of pathology (each group will be guaranteed a distribution of patients in RR or SP course representative of the incidence of the two courses in the Italian MS population) [55]. This will be a single-blind study.

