### 4.2. Outcomes

The primary outcomes of this study are the scores on the cognitive tasks and the scores on the gait and balance efficiency scales.

The secondary outcomes are the scores on the self-perception of cognitive deficits scale and on the self-perceived quality of life through the WHO-DAS.

The outcomes will be considered at T1 and T2.

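### Section 4.1 tests the arms against each other at T0, before randomisation, and does not name the group-by-time interaction or baseline adjustment that would give T0 a proper role

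*Protocol article*

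**What the plan says.** Four statements in the protocol article bear on this.

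- **Timing of T0.** Section 2.4: "After having completed the assessment procedures, the participants will be randomized to the three rehabilitation arms". Section 2.1 describes the T0 evaluation and continues: "Subsequently, patients will be assigned to one of the three conditions and will undergo rehabilitation treatment for a total of 12 weeks".
- **Between-group analysis.** Section 4.1 describes it as "comparing the results obtained by the groups at T0, T1, and T2 by performing an ANOVA between the scores of the cognitive assessments". A significant result leads to Bonferroni-corrected post hoc tests at p < 0.016. The same comparison is planned for anxiety, depression, self-perceived cognitive difficulty and perceived disability. The paragraph mentions no interaction, change score or baseline covariate.
- **Outcome visits.** Section 4.2: "The outcomes will be considered at T1 and T2".
- **Sample size.** Section 4.1 bases it on a power analysis "with a 0.30 effect size, power of over 0.95, and an alpha level of 0.05", described "as being sufficient for both repeated measures, within–between interaction Analysis of Variance (ANOVA"). The minimum is 48 patients, raised to 60 (20 per arm).

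**The concern.** No programme can have acted at T0, so a between-arm test there answers no question about treatment. Under sound randomisation every rejection is a chance finding. Section 2.2 already gives comparability of the groups as its reason for stratifying, so a small T0 p-value could easily be read as a failure of comparability. The article fixes no rule for what would follow.

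The wording also leaves the treatment test itself unclear. It could mean three separate ANOVAs, a group effect over all visits, or a group-by-time interaction. T0 is useless as a test in the first, harmful in the second and necessary in the third. At stake is whether the main comparison of the three programmes uses the baseline well, ignores it, or is weakened by it.

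**Working it through.** **Inputs.** From the article: 3 arms, 20 per arm, alpha 0.05, f = 0.30, minimum N = 48, seven MACFIMS tests (section 2.3). Assumed, because the article gives no values: unit SD, equal correlation ρ between visits, and arm means of 0, 0.5 and 1.0 SD at both T1 and T2. A count of 11 to 17 scores is also assumed.

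**1. The plan's own sample size.** For a within–between interaction with k groups and m measurements, λ = f²·N·m/(1−ρ), df1 = (k−1)(m−1) and df2 = (N−k)(m−1). With m = 2 and ρ = 0.5, λ = 0.09 × 48 × 2/0.5 = 17.28 on 2 and 45 df, giving power 0.958. N = 45 gives 0.945, so 48 is the minimum, as stated. The article gives neither m nor ρ. With m = 3 and ρ = 0.5 the minimum would be 39; m = 3 with ρ = 0.35 again gives 48. What matters here is that 48 belongs to an interaction test.

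**2. Reading A: one ANOVA per visit.** With K independent T0 tests, the chance of at least one rejection is 1 − 0.95^K. I also simulated equally correlated scores (3 × 20 patients, 20,000 runs, no allowance for stratification).

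| T0 scores tested | Independent | Correlation 0.3 | Correlation 0.5 |
|---|---|---|---|
| 7 (MACFIMS tests) | 0.30 | 0.28 | 0.24 |
| 11 (assumed) | 0.43 | 0.38 | 0.32 |
| 17 (assumed) | 0.58 | 0.50 | 0.39 |

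The T1 and T2 tests are unaffected by the T0 test. Their cost is that they ignore baseline. For a one-way comparison λ = n·Σ(d − mean d)²/v, with Σ(d − mean d)² = 0.5 in this scenario. Unadjusted at T1, v = 1 and λ = 20 × 0.5 = 10, so power is 0.79. With T0 as covariate, v = 1 − ρ²: 0.75 at ρ = 0.5 (λ = 13.3, power 0.90) and 0.51 at ρ = 0.7 (λ = 19.6, power 0.98).

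**3. Reading B: group main effect over T0, T1 and T2.** A difference d at both later visits becomes (0 + d + d)/3 = 0.67d. The variance of a mean of m visits is (1 + (m−1)ρ)/m. At ρ = 0.5:

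- Three visits: v = 0.667, λ = 20 × 0.5 × (4/9)/0.667 = 6.67, power 0.61.
- T1 and T2 only: v = 0.75, λ = 20 × 0.5/0.75 = 13.3, power 0.90.

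At ρ = 0.7 the powers are 0.53 and 0.86. The one-third loss is relative to the T1–T2 mean. Relative to the T1 effect it is larger if the effect fades: 0.8 SD at T1 and 0.4 SD at T2 give (0 + 0.8 + 0.4)/3 = 0.40, half the T1 value.

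**4. Reading C: group-by-time interaction.** T0 is the reference level. The interaction sum of squares per patient is 0.5 × 2/3 = 0.333, so at ρ = 0.5 λ = 20 × 0.333/0.5 = 13.3 on 4 and 114 df. Simulated type I error is 0.047 to 0.053.

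| Between-group test | Power, ρ = 0.5 | Power, ρ = 0.7 |
|---|---|---|
| Main effect over T0, T1, T2 | 0.61 | 0.53 |
| T1 alone, unadjusted | 0.79 | 0.79 |
| Mean of T1 and T2, unadjusted | 0.90 | 0.86 |
| Group-by-time interaction with T0 | 0.83 | 0.97 |
| T1 alone, T0 as covariate | 0.90 | 0.98 |
| Mean of T1 and T2, T0 as covariate | 0.98 | 1.00 |

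**The case against.** The best defence is that the trial was sized for a within–between interaction, in which T0 belongs, so the between-group sentence may be loose shorthand for that test. This stands in part: if the interaction is meant, there is no dilution and no surplus T0 test. But the interaction appears only in the power statement. The analysis text sets out two types of analysis and specifies repeated measures for the within-group one alone. If the interaction is intended, the sentence still misdescribes it.

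A second defence is that a T0 p-value is harmless, because section 4.2 confines outcomes to T1 and T2 and nothing in the article makes adjustment or exclusion depend on it. This also stands in part. The percentages in step 2 are chances of a meaningless baseline finding, not of a false treatment claim, and the risk of misreading is a judgement.

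Third, nothing in the text says that scores are averaged over visits, so reading B has the least support. That is fair, and its power loss is only one possible consequence.

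A reader might infer that the between-group analysis as a whole must either produce nothing but false positives or lose a third of the treatment effect. The documents do not support this. Per-visit tests at T1 and T2 are valid and undiluted, and the interaction is a third reading with support in the same section.

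**Conclusion.** The point holds in limited form. Section 4.1 makes a pre-randomisation visit a between-arm test, which conflicts with section 4.2, and it does not name the interaction on which the sample size rests. The T0 tests have about a 24 to 30% chance of at least one spurious rejection over seven cognitive tests, and about 32 to 58% over 11 to 17 scores. These figures assume a common correlation of 0 to 0.5 and ignore stratification, which could lower them somewhat. The fall in power from 0.90 to 0.61 applies only to a main effect over three visits under the assumed effects and ρ = 0.5.

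This does not invalidate the T1 and T2 comparisons. It should be corrected because the T0 test serves no objective and because the wording leaves open treatment tests whose power differs widely. Removing T0 altogether would be the wrong conclusion: as covariate it raises power at T1 from 0.79 to between 0.90 and 0.98 in the scenario shown.

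**What to change.** In the between-group paragraph of section 4.1:

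1. Remove T0 as a visit at which arms are tested, including the post hoc pairs. Report T0 scores by arm as means and SDs without p-values.
2. State one between-group test. Either compare the arms at T1 and T2 with the T0 score of the same measure as covariate, or declare the group-by-time interaction with T0 as reference level, followed by between-arm contrasts of change from T0 to T1 and T2.
3. Apply the same wording to anxiety, depression, self-perception and perceived disability.

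The interaction keeps the analysis aligned with the sample-size statement. If the covariate-adjusted comparison is chosen, the sample-size text should say how 60 patients serve that test. The cost is a few sentences; no further data, visits or patients are needed.
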